### **2.5 Rationale of the study**

The main strategy to avoid accidents of airway control is the planning and prediction of possible difficulties [7,8].

Although there are several scores on the prediction of difficulty for difficult intubation, there is little that exists regarding the class of patients with goiter [2,3,4,5,6].

The rationale is therefore to assess whether the predictive criteria of difficult intubation already validated for the population are also valid for the population suffering from thyroid disease, in addition to assessing whether there are peculiar characteristics of this population (neck diameter, tracheal displacement, mediastinal goiter) that can help in predicting the difficulty of intubation.

The study therefore aims to overcome the critical issues of previous studies both in terms of sample size, and as regards the overall analysis of parameters concerning difficult intubation without dwelling, unlike previous studies, only on some of them.

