#### **3.2. Secondary objective**

Identification of parameters or patterns of predictive parameters of difficult intubation during thyroidectomy.

The examination of NC/TMD for predicting DTI in patients undergoing thyroid surgery.

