## 5.2 Statistics

### 5.2.1 Sample Size

The estimates of study power and sample size were based on an assumption of a difference of 4% in the incidence of difficult intubation between the general population of patients undergoing surgery

[1] and the population of patients undergoing thyroid surgery [4], We use an  $\alpha$ -value of 5%, a power

( $1-\beta$  error) of 95%, a drop out percentage of 5%. The results of the analysis indicated that a sample size of 515 patients was necessary to estimate the prevalence of DTI in a population of patients undergoing thyroid surgery.

The data for each continuous variable will be analyzed for a normal distribution using the Kolmogorov-Smirnov test. Results for continuous variables with normal distributions will be expressed as mean (standard deviation) values; those with non-normal distributions will be expressed as median (interquartile range) values. Analysis of data with a normal or a non-normal distribution will be performed using the two-tail Student's t-test and the Mann-Whitney U test, respectively. The results for analyses of categorical variables will be reported as numbers (percentages) and were compared between groups using Chi-square tests. To determine the strength and direction of association between two variables, we will use the Bravais-Pearson's correlation test for variables with a normal distribution and Spearman's rank correlation test for variables that will not meet the assumptions of a normal distribution.

To determine the relationships between the dependent categorical variable (i.e., DTI) and one or more independent categorical variables (i.e., DTI predictors), we will perform a multiple logistic regression analysis to calculate odds ratios (ORs) with 95% confidence intervals (CIs). All statistical analyses will be performed using R version 3.4.0 (2017-04-21). P-values < 0.05 will be considered to indicate a statistically significant result.

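### Prediction objectives are answered only by odds ratios at p < 0.05, in a study sized for incidence that is small for modelling all listed parameters together

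*Protocol*

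**What the plan says.** Protocol section 3.2 sets two secondary aims. The first is "Identification of parameters or patterns of predictive parameters of difficult intubation during thyroidectomy". The second is to examine NC/TMD for predicting DTI. The abbreviations are not spelled out; I read them as the ratio of neck circumference to thyromental distance, and difficult tracheal intubation.

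Section 2.5 says the study will look at the parameters as a whole, "without dwelling, unlike previous studies, only on some of them". Section 5 lists 11 preoperative items for the data sheet. Thyromental distance is among them; neck circumference is not.

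Section 5.2.1 supplies the analysis: t or Mann-Whitney tests, chi-square tests, correlations, and then "we will perform a multiple logistic regression analysis to calculate odds ratios (ORs) with 95% confidence intervals (CIs". The number of predictors in that model is left open. The decision rule is "P-values < 0.05 will be considered to indicate a statistically significant result".

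The same section bases the sample size on "a difference of 4% in the incidence of difficult intubation between the general population of patients undergoing surgery" and thyroid surgery patients, and concludes that "a sample size of 515 patients was necessary to estimate the prevalence of DTI in a population of patients undergoing thyroid surgery". No calculation is given for the regression.

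**The concern.** There are two linked problems.

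- **The stated output does not answer the stated question.** An odds ratio with a p-value says whether a sign is associated with difficult intubation. It does not say how well the sign, or a combination of signs, separates difficult from easy cases, or whether predicted risks are right. No analysis named in section 5.2.1 tells the reader whether NC/TMD is a useful predictor.
- **The sample was sized for something else.** A joint model of all listed parameters would rest on few events for its size. Odds ratios would tend to be exaggerated, rare signs could separate the data, and a pattern found this way would look better in this sample than in new patients.

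The second section numbered 2.3 attributes the conflicting results of earlier thyroid studies to low numbers, and section 2.5 promises to overcome this. An overfitted model would risk repeating it.

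**Working it through.** **1. The plan's own figure.** Section 5.2.1 gives a 4-point difference, alpha 5%, power 95% and dropout 5%, but neither of the two rates, so 515 cannot be derived from its inputs alone. It is compatible with a one-sample test. For 6% against 10%, one-sided:

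n = [(1.645·√(0.06·0.94) + 1.645·√(0.10·0.90)) / 0.04]² ≈ 489, and 489/0.95 ≈ 515.

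Two-sided, 8.5% against 4.5% gives 493, then 519. Either way the calculation concerns incidence only. Evaluable patients: 515 × 0.95 = 489.25, taken as 489.

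**2. Degrees of freedom (df).** Of the 11 items in section 5, nine take one df each. Mallampati has four classes (3 df) and neck mobility three levels (2 df): 9 + 3 + 2 = 14. If both are dichotomised, the total is 11. Adding NC/TMD brings one more.

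**3. Events per df.** Events = 489 × rate.

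| Rate | Source | Events | Per df, 14 df | Per df, 11 df |
|---|---|---|---|---|
| 0% | lowest thyroid rate cited | 0 | 0 | 0 |
| 5% | assumption | 24.5 | 1.7 | 2.2 |
| 9% | assumption | 44.0 | 3.1 | 4.0 |
| 12.9% | highest thyroid rate cited | 63.1 | 4.5 | 5.7 |
| 20% | highest general-population rate cited (section 2.2) | 97.8 | 7.0 | 8.9 |

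The 5% and 9% rates are not in the protocol; they are illustrative and respect the 4-point gap. Excluding expected difficult intubation (section 4) should push events down.

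**4. Expected shrinkage.** S = 1 + P / [n·ln(1 − R²)], where P is the df and R² the Cox-Snell value, assumed at 15% or 30% of its maximum. The maximum is 1 − exp{2[p·ln p + (1 − p)·ln(1 − p)]}. At 5% it is 0.328, so R² = 0.15 × 0.328 = 0.0492, ln(1 − R²) = −0.0505, and S = 1 − 14/(489 × 0.0505) = 0.43. The n for S of at least 0.9 is P / [(0.9 − 1)·ln(1 − R²/0.9)].

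| Rate | S at 489, 14 df (R² 15% / 30% of max) | n for S ≥ 0.9, 14 df | df that 489 supports |
|---|---|---|---|
| 5% | 0.43 / 0.72 | 2,493 / 1,211 | 2.7 / 5.7 |
| 9% | 0.59 / 0.80 | 1,780 / 854 | 3.8 / 8.0 |
| 12.9% | 0.66 / 0.84 | 1,495 / 711 | 4.6 / 9.6 |

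With 11 df the loss scales by 11/14. Even in the most favourable cell, S = 1 − 0.16 × 11/14 = 0.87.

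**5. Simulation.** Maximum-likelihood fits with 14 df and n = 489, 300 runs per scenario, assumed predictor distributions, true AUC about 0.71:

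- At 5%: apparent AUC 0.78 against 0.64 in new data, median calibration slope 0.47, extreme or separated fits in about 41% of runs.
- At 9%: 0.76 against 0.66, slope 0.59, extreme or separated fits in about 13%.

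A second simulation, with 14 binary predictors of which four have a true OR of 2, gave apparent AUC 0.77 (5%) and 0.74 (9%) against 0.62 in new patients. Separation or failure to fit occurred in about 30% and 4%. The separation rates clearly depend on the assumed predictors.

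**6. False positives.** If no parameter predicts and tests are independent: 1 − 0.95¹¹ = 0.43 and 1 − 0.95¹⁴ = 0.51.

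**7. What can be shown.** Take one binary predictor with 30% prevalence, OR 3 and incidence 5%. Solving 0.7q + 0.3·3q/(1 + 2q) = 0.05 gives about 3.2% against 9.1%, in about 342 and 147 patients. Unadjusted two-sided power is 0.74. For OR 4 it is 0.89. At 9% incidence the values are 0.92 and 0.98. With 10% prevalence and OR 3, power is 0.59 (5%) and 0.75 (9%).

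**The case against.** The strongest reply is that the protocol does not commit to the model examined here. Section 5.2.1 leaves the number of predictors open and does not say the fit is unpenalised. The global look promised in section 2.5 could partly be met by the one-at-a-time tests. This stands: the 11 to 14 df are what follows if all listed parameters are analysed together, and a reader should not infer that an unpenalised 14-df model is prescribed.

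Second, variable selection, penalisation and validation are often left to a statistical analysis plan, which is not at hand. Their absence alone would be no finding. But section 5.2.1 already names the method, its output and the significance rule for these objectives, and that stated rule does not measure prediction.

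Third, a reader might infer that the study cannot show any parameter to matter. Step 7 contradicts this: common predictors with an OR of about 3 to 4 have reasonable power, though rarer or weaker ones do not.

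Fourth, a reader might blame the false-positive chance on scarce events. It is ordinary multiplicity, as step 6 shows. Nor should 24 to 44 events be read as the protocol's expectation; its cited thyroid rates allow 0 to 63.

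Finally, these are secondary aims of an observational study. That limits the consequence but does not remove the mismatch.

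**Conclusion.** The point holds in this form. The objectives ask about prediction, and the stated analysis delivers association. No sizing supports a joint model of all listed parameters. At 489 evaluable patients such a model has at most 4.5 to 5.7 events per df within the cited thyroid range, and about 1.7 to 4.0 at the assumed 5 to 9%. Expected shrinkage stays below 0.9 at the three rates in step 4 with either coding. A pattern from an ordinary fit would therefore look better than it is.

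The events-per-df figures rest on the cited or assumed rates and on all 11 items entering together. The shrinkage figures add an assumed R². The simulations add assumed predictor distributions and are illustrative. The 43 to 51% assumes independent tests and no true predictor. The primary incidence objective is not affected.

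**What to change.** Amend section 5.2.1 as follows:

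- Prespecify one multivariable model, with coding fixed in advance and no selection by p-value. Either limit it to the few df the expected events support (about 3 to 6 at 5%, 4 to 8 at 9%, under the R² assumptions above), or keep the wider set and fit it with Firth or ridge penalisation.
- Report bootstrap optimism-corrected AUC and calibration slope, repeating the whole fitting procedure in each resample.
- For NC/TMD, report AUC with 95% CI, and sensitivity and specificity at a cut-off that is prespecified or corrected for having been chosen from the data.
- Label p-values for individual predictors exploratory.
- State the expected number of events and the rate behind it.

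Amend section 5 to add neck circumference to the recorded parameters; otherwise the ratio cannot be computed. Section 4.1 limits recording to what a routine visit already collects, so confirm that the measurement fits that statement.

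The cost is a paragraph of text, one more item on the data sheet, and a few hours of analysis in R, which is already the planned software. No extra patients are needed. The downside is smaller odds ratios and a lower, more honest AUC.

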## **6. Risks and benefits for the patient**

The study is prospective observational. No clinical decision will be made based on the collected data. There are no direct benefits or risks added to those of a standardized clinical procedure.

## **7. Additional costs**

The study is prospective and observational study without additional costs.

## **8. Limitations of the Study**

The main limitation of the study is its monocentric nature.

## Annex 1 - Scale of Cormack and Lehane

[figure not shown]

Grade 1

[figure not shown]

Grade 2

[figure not shown]

Grade 3

[figure not shown]

Grade 4

Grade 1. Most of the glottis is visible

Grade 2. At least half of the glottis is visible

Grade 3. The glottis is not visible, only the epiglottis

Grade 4 is visible. language base

## Annex 1 - Mallampatiscale

[figure not shown]

Class I: soft palate, uvula and visible pillars.

Class II: visible palate and uvula.

Class III: soft palate and visible uvula base.

Class IV: only the hard palate is visible.
